## Discussion

Mimicking a viral infection by activating pattern recognition receptors (PRR) of the innate immune system is an interesting therapeutic approach, tested for a variety of indications [1, 15, 16]. Apart from the toll-like receptor family, the retinoic acid inducible gene-I (RIG-I) is a particular promising candidate for this strategy. RIG-I is suggested as drug target in a broad range of indications including viral infections, cancer and autoimmune disease such as multiple sclerosis [1]. RIG-I is ubiquitously expressed in non-malignant but also malignant cells and leads not only to the release of antiviral cytokines (e.g. type I IFN) and NK cell activation but also to apoptosis induction in cancer but not in non-malignant cells [7–11]. Moreover, RIG-I activation can suppress a T(H)17 response *in vivo* [12]. Thus, the immediate and comprehensive immune response orchestrated by RIG-I seems to be of great potential in a variety of diseases with a still unmet medical need. But it needs to be taken into account that all these mechanisms of actions are not only beneficial but can also cause side effects depending on the dose. Therefore, the immune activation by RIG-I needs to be sufficiently understood and well balanced. The disastrous outcome of the TeGenero trial unintentionally demonstrated the consequences of an underestimated activating immune effect leading to a cytokine storm [17]. As a consequence the EMA released a guideline describing risk factors to be considered before starting a first-in-human phase I trial (EMEA/CHMP/SWP/28367/07). As the RIG-I ligand represents a new mode of action, is activating in nature and turns on different immune pathways, this therapeutic approach has multiple aspects of high risk compounds. Therefore, the preclinical data need to be gathere carefully and scientifically driven to obtain a comprehensive understanding of the potential outcomes of the RIG-I ligand administration. To further reduce the risk of the upcoming phase I studies with the new RIG-I ligand, we decided to design a clinical study to add human *in vivo* data that are suitable to function as a biomarker for the immune activation induced by RIG-I. To this end, we will comprehensively measure the immune response induced by standard treatment with recombinant IFN-β, including protein and mRNA expression of known IFN-β dependent genes (e.g. CXCL10, MxA, RIG-I), miRNA expression pattern, genome wide mRNA expression. In the subsequent phase I studies with the RIG-I ligand these information will be used to judge whether the induced type I IFN is below or above standard treatment with recombinant IFN-β. In addition, as emotional changes are described for type I IFN [18–21], we will perform functional MRI scans to screen for early effects in order to learn how this side effect can be detected early upon exposure to a RIG-I ligand. Therefore, the study presented here will provide crucial data to safely guide the application of the RIG-I ligand. To rule out differences in the response to IFN-β we will include both healthy volunteers as the first population within the clinical testing being exposed to the RIG-I ligand as well as patients with relapsing-remitting multiple sclerosis as patients meant to be treated with the RIG-I ligand later in development. Although numerous effects of type I IFN on the immune system are well established since decades, the results from the literature cannot be used here for different reasons: data obtained in animal or *in vitro* systems do not necessarily reflect the *in vivo* situation in humans, the complete set of read outs were not investigated in a single comprehensive study, it is unclear how repeatable the assays are that were used, and studies were often done in patients but not healthy volunteers with confounding factors such as concomitant medications. In addition, potential adverse neurological drug effects have to be assessed *in vivo* in humans without confounding factors of neurological disease symptoms. Therefore, a lot of emphasis is laid on the quantitative measurement of potential emotional or cognitive changes due to the exposure to IFN-β in healthy humans using MRI techniques. To be technically able to transfer the results in the biomarker study to the phase I studies with the RIG-I ligand, the main read outs used here (ELISA and qPCR) will be validated on repeatability, precision, pre-assay effects, dilution linearity and adequate controls and standards will be generated and included that can be used for comparison in future studies. Nevertheless, information obtained here will bear certain limitations: activation of RIG-I leads to a profound induction of type I IFN but also induces additional pathways and cytokines such as pro-inflammatory cytokines (e.g. IL-6) and IFN-γ (unpublished data) not mimicked by application of IFN-β alone. Additionally, the time course of type I IFN induction caused by activation of RIG-I is not necessarily mirrored by application of the recombinant protein. Therefore, the results of this biomarker study need to be interpreted in connection with the complete preclinical program and are not meant to substitute for it. But taking these limitations into account, this study is a rare, maybe unique approach to define biomarkers in the human system *in vivo* that increases the safety of the clinical development of a drug before the actual compound is given the first time to healthy subjects. The data obtained here can be additionally used to guide other treatments also involving induction of type I IFN, such as ligands for TLR7 or 9 (as intended effect or unwanted side effect, e.g. siRNA) [15, 16, 22, 23]. Therefore, this study proposes a way, how the safety of a first-in-man phase I clinical trial can be enhanced in addition to the principles outlined in the current guidelines of drug development. As additional benefit, this study is suitable to find new factors being induced by type I IFN in the human system *in vivo*, namely in- or decreased miRNA, since studies investigating the effects of type I IFN in a very controlled human *in vivo* system in healthy volunteers are rare.

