
For this purpose, the ResI study was set up as a clinical trial aiming to establish a biomarker for the safety and efficacy of the RIG-I ligand, a novel therapeutic entity currently in preclinical testings. Since studies of the RIG-I ligand will start in healthy volunteers and will be continued in MS patients both populations are included in this study as they could show significant differences in response to IFN-β. Additionally, this comprehensive, prospective analysis of the IFN-β dependent immune activation and changes in miRNA expression in this controlled setting will help to understand the physiological response to IFN-β in healthy volunteers and in MS patients.

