### Secondary objectives

Secondary objectives of this trial are the analysis of the miRNA- and gene-expression pattern in response to recombinant IFN-β in peripheral blood mononuclear cells and serum of healthy volunteers as well as RRMS patients, the comparison of the response to IFN-β between healthy volunteers, patients with RRMS naïve to IFN-β treatment and RRMS-patients with established IFN-β treatment, correlation of side effects of IFN-β treatment with immune- or miRNA-response to IFN-β. Potential central nervous adverse drug effects such as emotional changes associated with IFN-β treatment (depression, anxiety, impulsivity) will be assessed by psychometric testings and noninvasive neuroimaging techniques.

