### Statistical analysis

The **sample size** is set on 20 healthy volunteers and 20 patients with established IFN-β treatment and 10 MS patients naïve to IFN-β treatment. Since this is a study to gain information about the distribution of the expression values in these patients, this sample size is not based on statistical considerations.

**Primary target variables** of the study is the estimation of changes in serum level of type I IFN and type I IFN-dependent proteins (e.g. CXCL10) as well as of changes in mRNA expression of type I IFN-dependent genes (e.g. CXCL10, MxA and RIG-I) after a dose of IFN-β treatment in healthy volunteers and in patients with RRMS. For this purpose, the median of the levels will be calculated separately for the two study groups. 95 % confidence intervals for the medians will be calculated using bootstrap. As additional descriptive parameters mean, standard deviation, minimum, maximum and the quartiles of the distribution will be calculated for each group and variable. A comparison of the expression levels between patients and controls will be performed with a two-sided Mann–Whitney-Wilcoxon test. These tests are regarded as descriptive analysis, their result are reported as p-values.

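### The Discussion says both populations are enrolled to rule out differences in response, but the only between-group output stated is a descriptive p-value, which cannot bound a difference at these group sizes

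*Protocol article*

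**What the plan says.** The Discussion gives the reason for enrolling two populations: "To rule out differences in the response to IFN-β we will include both healthy volunteers", as the first people to be exposed to the RIG-I ligand, together with RRMS patients, for whom it is meant later.

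Two other places are more modest. The Background says that "both populations are included in this study as they could show significant differences in response to IFN-β". Under Secondary objectives the aim is "the comparison of the response to IFN-β between healthy volunteers, patients with RRMS naïve to IFN-β treatment and RRMS-patients with established IFN-β treatment".

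The Statistical analysis section sets the group sizes at "20 healthy volunteers and 20 patients with established IFN-β treatment and 10 MS patients naïve to IFN-β treatment" and adds that "this sample size is not based on statistical considerations". For each group it plans a median, for which 95% "confidence intervals for the medians will be calculated using bootstrap", along with mean, standard deviation, range and quartiles. Between groups it says: "A comparison of the expression levels between patients and controls will be performed with a two-sided" Mann–Whitney–Wilcoxon test, and then "These tests are regarded as descriptive analysis, their result are reported as p-values". It names no estimate of the between-group difference, no interval for it and no margin.

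**The concern.** Ruling out a difference means showing that it is smaller than some stated size, which takes an upper bound: an interval for the difference. A test of no difference gives none. Its p-value measures how surprising the data would be if the groups were alike, and in small groups a large p-value is expected even when they are not alike. The stated purpose and the stated output therefore do not match.

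The between-cohort comparison is a secondary objective. If its result is a p-value alone, a non-significant one gives readers no direct measure of how large a difference remains possible, and the Discussion's wording invites them to take it as similarity. This matters because the data are meant to help guide dose steps in the later ligand studies, which will move from volunteers to MS patients.

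**Working it through.** **Inputs from the document.** Groups of 20 healthy volunteers, 20 RRMS patients on established treatment and 10 RRMS patients starting treatment; a two-sided rank test of patients against controls. The Statistical analysis section speaks of two study groups although three cohorts are enrolled, so three contrasts are possible: 20 v 20, 20 v 10, and 20 v 30 if patients are pooled.

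**Assumptions.** The document gives no SD, effect size, significance level or margin, so there is no planned figure to reproduce. I assume normal data with equal spread, a two-sided 5% level, and differences measured in SD units (on the log scale if the analyte is analysed that way).

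**Chance that the test misses a true shift d.** The large-sample approximation is Φ(1.96 − d·√(0.955/(1/n₁+1/n₂))), where 0.955 = 3/π is the efficiency of the rank test under normality. For d = 0.8:

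- 20 v 20: 0.8·√(0.955/0.100) = 2.47, so Φ(−0.51) ≈ 30%
- 20 v 10: 0.8·√(0.955/0.150) = 2.02, so Φ(−0.06) ≈ 48%
- 20 v 30: 0.8·√(0.955/0.0833) = 2.71, so Φ(−0.75) ≈ 23%

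The approximation is slightly optimistic in samples this small. Simulation of the test itself (10,000 or more trials per scenario) gives these shares of non-significant results:

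| True shift | 20 v 20 | 20 v 10 | 20 v 30 |
|---|---|---|---|
| 0.5 SD | 68% | 78–80% | 62% |
| 0.8 SD | 33% | 53% | 25% |
| 1.0 SD | 15% | 35% | 10% |
| 1.2 SD | 5% | 19% | 2% |

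These figures move by one or two percentage points with the simulation run and, at 20 v 10, with the choice of exact or asymptotic p-value.

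**Width of an interval for the shift.** The approximate 95% half-width of the Hodges–Lehmann estimate is 1.96·√((1/n₁+1/n₂)·π/3):

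- 20 v 20: 1.96·√(0.100·1.047) = 0.63 SD
- 20 v 10: 1.96·√(0.150·1.047) = 0.78 SD
- 20 v 30: 1.96·√(0.0833·1.047) = 0.58 SD

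A t-interval gives 0.64, 0.79 and 0.58 SD. The Hodges–Lehmann formula is a large-sample one, so realised intervals may be somewhat wider, chiefly where one group has 10.

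**What a non-significant result leaves open.** If the two groups matched exactly at 20 v 20, the interval would still run from about −0.63 to +0.63 SD. If the p-value fell just above 0.05, it would run from about 0 to 2 × 0.63 = 1.26 SD (2 × 0.78 = 1.56 SD at 20 v 10; 2 × 0.58 = 1.16 SD at 20 v 30). The p-value alone leaves a reader to work out where in that range the data lie.

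**Whether the per-group intervals fill the gap.** In simulation the bootstrap 95% interval for a median has a half-width of about 0.53 SD with 20 subjects and 0.72 SD with 10. Two such intervals overlap until the medians differ by about 0.53 + 0.53 = 1.06 SD (20 v 20) or 0.53 + 0.72 = 1.25 SD (20 v 10). Overlap therefore does not bound the difference either.

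**The case against.** The best reply is that this is one loosely worded sentence in a Discussion. The Background expects that differences may exist, the formal objective is a comparison, and the tests are called descriptive. On that reading the authors mean to look for population differences, not to prove equivalence. This stands: the document plans no equivalence conclusion, and the point concerns an overstated aim and an output that does not serve it.

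Three further replies also stand in part. The plan reports more than p-values: medians with intervals and full descriptives will show roughly how far apart the groups are, though without an interval for the gap. The test is not blind to large effects, since a 1.2 SD shift is detected in about 95% of trials at 20 v 20, 81% at 20 v 10 and 98% at 20 v 30. And the choice of interval method is often left to an analysis plan, which is not shown here. But the article itself states what the between-group comparison will report, and that can be judged against the purpose it gives.

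A reader might go further and infer that a healthy-volunteer benchmark will be carried over to patients on the strength of a non-significant test. The document does not say so. It plans separate estimates for the study groups, and it states no decision rule or similarity conclusion.

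**Conclusion.** The concern holds in limited form. The between-group output stated in the Statistical analysis section cannot support the purpose stated in the Discussion. Shifts of about 0.8 SD would go undetected in a quarter to a half of trials, depending on the contrast, and even perfectly matching groups could not exclude differences below roughly 0.6 to 0.8 SD. Very large shifts would usually be seen.

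All sizes rest on normal data, equal spread and a two-sided 5% level, none of which the document gives. Skewed analytes would change the figures, but not the logic that a non-significant p-value sets no upper bound on a difference. The remedy is one of wording and reporting. The design of a descriptive study with group sizes chosen without a power calculation need not change.

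**What to change.** 1. For each between-cohort comparison, report the Hodges–Lehmann shift (or the ratio, if analysed on the log scale) with its 95% confidence interval, alongside the descriptive p-value. Name the cohorts in each comparison, so that it is clear whether patients are pooled.
2. In the Discussion, change *to rule out differences* to *to estimate differences*, in line with the Background and Secondary objectives.
3. State that similarity will not be concluded from a non-significant p-value.

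An equivalence margin is not required. It would add a confirmatory criterion to an expressly descriptive study, and one that these groups could meet with 80% power only at wide margins: about 0.93 SD at 20 v 20, 1.13 SD at 20 v 10 and 0.84 SD at 20 v 30, using two one-sided 5% tests with no true difference.

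The cost is one standard output and a more modest claim, with no additional participants.

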
## Abbreviations

MS: multiple sclerosis
RRMS: rapid-relapsing multiple sclerosis
IFN: Interferon
IFN-β: Interferon-beta
EDSS: Expanded disability status scale
ECG: Electrocardiogram
MRI: Magnetic resonance imaging
RIG-I: Retinoic acid inducible gene-I
PRR: Pattern recognition receptor
3pRNA: 5’-triphosphorylated RNA
EMA: European Medicines Agency
